### Blinding

2.8

Blinding procedures are implemented for both participants and trial staff to minimize potential bias and ensure the validity of the study results.

For participants, blinding is achieved by providing all individuals with the same QR code to access the mini program. Upon scanning, participants are randomly assigned to either the intervention or control content within the same program interface, without any indication of their group allocation. Both intervention and control participants access the same mini program, with only the internal content differing based on group assignment. This setup ensures that participants remain unaware of their specific allocation, thus preserving blinding at the participant level.

For trial recruitment and management staff, including obstetricians, nurses, and the statistician responsible for data analysis, blinding is also maintained to prevent any inadvertent influence on study outcomes. Trial staff are blinded to each participant’s group assignment. All study results will be analyzed and interpreted in a blinded manner to reduce the risk of biased interpretation.

### Sample size determination

2.9

In this study, to detect a medium effect size (d=0.37) for a two-tailed independent t-test at a significance level of 5% with a power of 80%, at least 115 participants are required for each group (29). Taking into account a loss to follow-up of 20% in our study, the total sample size required at baseline for the RCT is 290 (145 per group). It is assumed that approximately 30% of women will decline or be ineligible to participate; we plan to approach at least 415 pregnant women at the hospital antenatal clinic. G*Power software was used for the sample size calculation.

### Statistical analysis

2.10

We will descriptively summarize participants’ baseline characteristics, outcome variables, satisfaction levels and adverse events. Independent t-tests or Mann-Whitney U tests will be performed to compare continuous variables, and chi-square or Fisher’s exact tests will be applied for categorical characteristics. To account for the correlation of repeated measures from the same participant, generalized linear models with random effects (participants) will be fitted to evaluate the intervention effect on outcome variables over time, adjusting for potential confounders such as age, parity, and family history of mental disorders.

Outcome analyses will be conducted on both the intention-to-treat population, which includes all randomized participants, and the per-protocol population, consisting of eligible participants who adhere to the planned intervention and follow ups. Missing data for primary and secondary outcomes will be imputed using the last value carried forward method in the intention-to-treat analysis. Additionally, to assess the impact of intervention adherence, adherence metrics—such as daily task completion rates and module progression—will be incorporated into sensitivity analyses. Participants will be stratified based on their engagement levels, and adherence data will be included as exploratory covariates in the regression models. These analyses will help determine whether engagement level influences intervention effectiveness and whether adherence plays a moderating role in treatment outcomes.

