### Outcomes

2.7

Primary outcomes include changes in EPDS, PHQ-9 and GAD-7 scores from baseline (T_0_) to 6 weeks postpartum (T_2_).

The secondary outcomes include: (i) changes in EPDS, PHQ-9 and GAD-7 scores from baseline (T_0_) to post-intervention (T_1_), and (ii) comparisons of CSQ-8 results and the number of adverse events post-intervention (T_1_) between the intervention and control groups.

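### The analysis section names covariates but not the outcome's own baseline score, and does not tie the model's treatment estimate to six weeks postpartum (T2), so it may forgo precision that is free to take

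*Protocol article*

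**What the plan says.** Protocol article, Outcomes (2.7): "Primary outcomes include changes in EPDS, PHQ-9 and GAD-7 scores from baseline" to T2, six weeks postpartum. The same section makes change to the end of the intervention (T1) secondary. The closing paragraph of the Introduction also names six weeks postpartum as the primary time.

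Statistical analysis (2.10) describes two kinds of comparison:

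- "Independent t-tests or Mann-Whitney U tests will be performed to compare continuous variables".
- A random-effects model for repeated measures, used to evaluate the intervention effect over time, "adjusting for potential confounders such as age, parity, and family history of mental disorders".

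Section 2.10 does not mention the baseline score, say whether baseline enters the model as a response, or name an arm-by-visit term or a T2 contrast.

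Section 2.4 and Table 1 show that the baseline values exist: EPDS at recruitment, PHQ-9 and GAD-7 in the baseline questionnaire. Sample size determination (2.9) plans "to detect a medium effect size (d=0.37) for a two-tailed independent t-test" "at a significance level of 5% with a power of 80"%.

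**The concern.** The baseline value of a symptom scale is usually among the strongest predictors of its later value. Section 2.10 picks out three prognostic covariates and leaves that one unnamed. A raw change score subtracts the whole baseline value, so it carries baseline measurement noise into the comparison. Allocation in section 2.3 is simple and unstratified, so the design does nothing to balance baseline severity between arms; only the analysis can.

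The second gap is that the model is said to assess an effect over time, while the primary outcome belongs to one visit. Section 2.10 does not say which model term answers the primary question. Nor does it say whether the model or the t-test is the primary analysis, and the sample size rests on the t-test. At stake are the width of the confidence interval and some freedom of choice after the data are seen.

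**Working it through.** **The plan's own figure.** For d = 0.37, two-sided alpha 0.05 and 80% power, the normal approximation gives n = 2(1.960 + 0.842)²/0.37² = 114.7, so 115 per group. The exact t-test gives 115.6, so 116. Allowing for 20% loss, 115/0.8 = 143.75 (144) and 116/0.8 = 145 per group, or 288 to 290 in total. The stated "at least 115 participants are required for each group" and the total of 290 therefore reproduce.

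**Relative variances.** Let r be the baseline-to-T2 correlation. The document does not give it, so it is an assumption here. With equal SDs, and the T2 score alone set to 1:

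- change score: 2(1 − r)
- baseline-adjusted T2 score: 1 − r²
- ratio, adjusted to change: (1 − r²)/[2(1 − r)] = (1 + r)/2

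| r | change | adjusted | ratio |
|---|---|---|---|
| 0.3 | 1.40 | 0.91 | 0.65 |
| 0.4 | 1.20 | 0.84 | 0.70 |
| 0.5 | 1.00 | 0.75 | 0.75 |
| 0.7 | 0.60 | 0.51 | 0.85 |

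**Does the repeated-measures model already achieve this?** A generalized least squares check used a random-intercept model with baseline, T1 and T2 all as responses. With a free group difference at baseline, the T2-minus-baseline contrast has variance 1.40, 1.00 and 0.60 at r = 0.3, 0.5 and 0.7, the same as the change score. With baseline means constrained equal, the T2 contrast has 0.91, 0.75 and 0.51, the same as baseline adjustment. The answer therefore turns on a detail that section 2.10 does not state.

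**In terms of power, 115 per group (normal approximation).**

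- If d = 0.37 is in T2-score SD units, change score against adjusted: 66.0% and 83.7% at r = 0.3; 72.6% and 86.5% at r = 0.4; 80.1% and 90.0% at r = 0.5; 95.2% and 97.6% at r = 0.7.
- If d = 0.37 is in change-score SD units, the change-score test has 80.1% at any r. Adjustment gives 93.6%, 91.8%, 90.0% and 86.1% at the same four values.

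**EPDS separately.** Section 2.2 restricts baseline EPDS to 5-12, so its baseline SD is smaller than its T2 SD. Assume 2.3 at baseline and 4.5 at T2 (neither is in the document). Change variance is 2.3² + 4.5² − 2r(2.3)(4.5) = 25.54 − 20.70r; adjusted variance is 20.25(1 − r²).

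- r = 0.2: 19.44/21.40 = 0.91
- r = 0.4: 17.01/17.26 = 0.99
- r = 0.5: 15.19/15.19 = 1.00

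The gain is thus 0-9%. A second assumption, a normal score with mean 8 and SD 4.5 truncated to the entry range (restricted SD about 2.2), gives 4-11% against change for unrestricted r of 0.3 to 0.7. PHQ-9 and GAD-7 have no entry limits of their own, so the equal-SD table is the more relevant guide for them.

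**The case against.** The strongest reply is that this is silence in a condensed article, not a wrong choice. Much of that stands, and it rules out several stronger readings that a reader might infer.

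- *The plan excludes the baseline score.* It does not. The covariates are given as examples, so the list is open.
- *Precision is certainly lost.* Not so. The outcome is a change from baseline and the model is for repeated measures, so baseline may enter as a response. If the baseline means are then held equal, nothing is lost.
- *The trial does not target T2.* Section 2.7 and the Introduction both fix T2. Only the model description fails to link to it. A reader might suppose a single arm effect averaged over all visits, which would dilute the T2 effect, but the document never describes such a model.
- *The primary outcome will be tested by t-test.* The sentence on two-sample tests follows a descriptive summary, and the model is the only method said to evaluate the intervention effect. But outcome variables are in that summary and section 2.9 is built on a t-test, so the ambiguity is real.
- *Power falls short of plan.* The 72.6% at r = 0.4 requires d in T2-score SD units. On the change-score SD the planned test keeps its 80%.

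The power figures also treat 115 per group as complete cases. They do not describe the intention-to-treat analysis with last values carried forward.

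What the reply does not remove: the article goes as far as naming tests, a model class and covariates, and as written these permit the less precise analysis.

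**Conclusion.** The point holds as a matter of precision and clarity. Section 2.10 names neither the baseline score nor the T2 contrast. Two natural ways of carrying it out (an unadjusted change score, or a free group difference at baseline) are less efficient than baseline adjustment for any r below 1 at equal SDs. For PHQ-9 and GAD-7 the adjusted variance would be about 0.65 to 0.85 of the change-score variance for assumed r of 0.3 to 0.7. For EPDS the gain is small, about 0-9% under the assumed SDs. Every size given here rests on correlations and SDs that the document does not supply. The consequence is not bias, not an inflated Type I error and not a sample size error. The change is worth making because it costs almost nothing.

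**What to change.** In section 2.10, or in the analysis plan before unblinding:

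1. State that the random-effects model is the primary analysis for each scale.
2. Either include the baseline score of the same scale as a covariate, with T1 and T2 as responses, or keep baseline as a response and constrain the group means there to be equal. State which.
3. Include arm, visit and an arm-by-visit term.
4. Define the primary estimate as the arm difference at T2 with its 95% CI; the T1 difference from the same model is secondary.
5. Keep the t-test or Mann-Whitney comparison as supportive.

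The cost is analysis wording. All the variables are already collected, and no visit, questionnaire or participant is added. The stated sample size can stand.

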### Participants

2.2

Pregnant women meeting the following inclusion criteria will be invited to participate in the study: (1) aged 18-45 years, (2) at 20-24 weeks of gestation, (3) at risk of depression but not experiencing severe depressive symptoms at recruitment, as indicated by an Edinburgh Postnatal Depression Scale (EPDS) score ranging from 5 and 12 (17), (4) own a smartphone, and (5) are able to independently engage with the program.

Pregnant women will be excluded from the study if they meet any of the following criteria: (1) have serious medical conditions or pregnancy complications that may affect their psychological condition, as determined by their medical doctor, (2) have a prior diagnosis of any mental disorders, (3) are currently or were recently (within the past six months) receiving any kinds of psychological services or treatments, (4) have a history of self-harm or suicide, (5) have any suicidal thoughts in the past 12 months, (6) experienced fetal deaths in the past 18 months.

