The PHQ-9 is a widely used self-administered instrument for diagnosing and assessing the severity of depression. Patients rate the frequency of specific depressive symptoms experienced over the past two weeks on a four-point scale, ranging from “not at all” to “most days”. Total scores range from 0 to 27, with a score of 10 or greater being the most common cut-off for screening major depressive disorder (19). Studies conducted in mainland China have validated the reliability and validity of the Chinese version of the PHQ-9 in detecting major depression (24, 25).

The GAD-7 is a valid self-assessment tool used to measure anxiety symptoms over the past 14 days. It consists of seven items, each rated on a score from 0 to 3. The total score ranges from 0 to 21, with higher scores reflecting more severe anxiety symptoms. Scores between 5 and 9 suggest mild anxiety, and a score greater than 14 indicates severe anxiety (20). In our study, the Chinese version of GAD-7 is applied (26).

The depressive and anxiety symptoms will be measured at follow ups, with all participants asked to complete the EPDS, PHQ-9 and GAD-7 after the 8-week intervention period, and again at 6 weeks postpartum. The use of both EPDS and PHQ-9 allows for a more comprehensive assessment of depressive symptoms, as EPDS is specifically designed for perinatal populations and captures unique features such as anxiety and guilt, while PHQ-9 aligns with DSM-based diagnostic criteria, facilitating comparisons with broader clinical and research settings. This dual approach ensures a more nuanced evaluation of depression severity and symptom patterns in our study population. In addition, an acceptability survey will be administered to assess participant satisfaction level post-intervention. For participants who do not complete the project, their reasons for withdrawal will be gathered through a brief questionnaire.

In this study, we will use the Client Satisfaction Questionnaire (CSQ-8) to assess participant satisfaction with the intervention (27). The CSQ-8 is a widely used, standardized tool designed to measure client satisfaction with healthcare services and interventions. It consists of 8 items, each scored on a Likert scale, with higher scores indicating greater satisfaction. The questionnaire covers aspects such as perceived quality of service, the extent to which the service met participants’ needs, and their overall satisfaction with the experience.

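### Last value carried forward in the intention-to-treat analysis puts pregnancy scores in place of missing 6-week postpartum scores, with a bias whose size and direction the protocol cannot fix

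*Protocol article*

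**What the plan says.** The protocol article (Statistical analysis) fixes the method for incomplete data: "Missing data for primary and secondary outcomes will be imputed using the last value carried forward method in the intention-to-treat analysis". It applies to "the intention-to-treat population, which includes all randomized participants". The same section plans a longitudinal model: "generalized linear models with random effects (participants) will be fitted to evaluate the intervention effect on outcome variables over time".

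The Outcomes section defines the primary outcomes as changes in EPDS, PHQ-9 and GAD-7 from T0 to T2, which is 6 weeks postpartum. Women enter "at 20-24 weeks of gestation" (Participants), and the follow-up scores are taken "after the 8-week intervention period, and again at 6 weeks postpartum" (Data collection and measurements). The sample size section expects substantial loss: "Taking into account a loss to follow-up of 20% in our study".

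The only analyses labelled as sensitivity analyses concern adherence metrics, which "will be incorporated into sensitivity analyses". None addresses missing scores.

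**The concern.** T0 falls at 20-24 weeks of gestation and T1 eight weeks later, at about 28-32 weeks. Barring a very preterm birth, every value that can be carried to T2 is a pregnancy score. Carrying it assumes that nothing changes across delivery, although postnatal symptoms are the trial's stated main objective. If T0 is carried, the change is zero by construction. For EPDS, the carried baseline also lies within the eligibility band of 5 to 12.

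Two further consequences follow. The filled-in values enter the analysis as if observed, so the standard error ignores that they are guesses. Also, a participant random-effects model fitted to the observed scores can already use incomplete records under missing at random; filling in first gives that up. At stake is the primary estimate for all three primary outcomes.

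**Working it through.** **The plan's own figure.** For d = 0.37, two-sided 5% and 80% power, n = 2 × (1.96 + 0.84)² / 0.37² = 115 per group. The exact t calculation gives 116. Allowing for 20% loss, 115/0.8 = 144 and 116/0.8 = 145. The stated 115 and 145 per group reproduce. The expected loss is 0.20 × 290 = 58 women, 29 per arm.

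**Assumptions not in the protocol.** These are unit SD at each visit and correlation 0.5 between visits (so the SD of change is 1); the share f of lost women who leave before T1 and so carry T0; the ratio r of the T1 effect to the T2 effect; the common shift in scores over time; and the split of loss by arm.

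**Equal loss, true effect 0.37.** With a share m missing T2 in both arms, the effect expected under last value carried forward (LOCF) is

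0.37 × [(1 − m) + m(1 − f)r], with m = 0.20.

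| Who is carried | f | r | Expected effect |
|---|---|---|---|
| All T0 | 1 | any | 0.37 × 0.80 = 0.296 |
| Half T0, half T1 | 0.5 | 1 | 0.37 × 0.90 = 0.333 |
| All T1, smaller T1 effect | 0 | 0.5 | 0.37 × 0.90 = 0.333 |
| All T1, same effect | 0 | 1 | 0.37 × 1.00 = 0.370 |
| All T1, larger T1 effect | 0 | 1.5 | 0.37 × 1.10 = 0.407 |

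Simulation with 145 per arm agrees with these values. With equal loss and no true effect, the rejection rate stays at about 5%.

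**Unequal loss, no true effect.** Let s be the common shift from T0 to T2 and s1 the part of it complete by T1. The false difference is

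(difference in loss) × [f·s + (1 − f)(s − s1)].

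With s = 0.5 SD:

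| Loss by arm | f | Shift complete by T1 | False difference (SD) | Type I error |
|---|---|---|---|---|
| 30% vs 10% | 1 | any | 0.20 × 0.5 = 0.10 | about 15% |
| 30% vs 10% | 0.5 | none | 0.20 × 0.5 = 0.10 | about 14-15% |
| 30% vs 10% | 0.5 | half | 0.20 × 0.375 = 0.075 | about 10% |
| 30% vs 10% | 0.5 | all | 0.20 × 0.25 = 0.05 | about 7% |
| 25% vs 15% | 1 | any | 0.10 × 0.5 = 0.05 | about 7% |
| 25% vs 15% | 0.5 | half | 0.10 × 0.375 = 0.0375 | about 6-7% |

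For the first row, a carried T0 has change zero and no variance. The variances of change are 0.7 + 0.7 × 0.3 × 0.5² = 0.7525 and 0.9 + 0.9 × 0.1 × 0.5² = 0.9225. The SE is √[(0.7525 + 0.9225)/145] = 0.1075, and 0.10/0.1075 = 0.93 standard errors, which gives a rejection rate of about 15%. If every lost woman carries T1 and the shift is complete by then, the false difference is zero even at 30% versus 10%.

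**The alternative.** Likelihood estimation from the observed scores was simulated in the same framework, with about half of the lost women leaving before T1. It recovered the true effect (0.368 to 0.372) and gave about 0.00 under no effect. In a run where women with higher last scores were more likely to leave (nominal 30% versus 10%, half the shift by T1), LOCF gave a false 0.112 SD with type I error 15.8%; the likelihood estimate was again 0.00.

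**The case against.** The strongest reply is that little harm is shown at the plan's own figure. With 20% lost in each arm, type I error is not inflated, and the usual result is some attenuation. This stands, and it limits several stronger readings that a reader might infer.

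- *LOCF always shrinks the effect, so it is at least conservative.* The first table shows no bias or an increase when T1 is carried, and unequal loss can create a difference in favour of either arm.
- *Power falls to about 71%.* That figure takes 0.296 with the SD held at 1. Under the assumptions above, carrying T0 also shrinks the variance: the SE is about √[(0.80 + 0.82)/145] = 0.106, 0.296/0.106 = 2.8, and power is about 80%. The firmer criticism is a distorted estimate and a standard error that treats guesses as data.
- *The two programmes invite unequal dropout.* The Matched attention control section gives the control arm brief daily tasks built to mirror the intervention's structure and engagement, and the Blinding section describes one shared interface. Stopping app tasks is also not the same as missing the T2 questionnaire. Unequal loss is possible, but the documents do not point to it.
- *The random-effects model is abandoned.* The text keeps it. What is lost is its ability to handle incomplete records.
- *The EPDS eligibility band constrains every carried score.* It applies to EPDS alone, and only when T1 is missing as well.

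Two possible rescues do not succeed. A separate analysis plan may exist, but the protocol states LOCF as its method, so this is a choice and not an omission. The per-protocol analysis selects women on adherence and completed follow-up, so it cannot check the intention-to-treat result.

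**Conclusion.** The point holds. LOCF is a stated choice that replaces a missing postpartum score with a pregnancy score for up to about 58 women, and no other named analysis handles missing scores adequately. At equal 20% loss, a true 0.37 SD effect is estimated at anything from about 0.30 to 0.41, with no type I inflation. With an assumed 30% versus 10% loss and a 0.5 SD shift, the false difference is mostly 0.05 to 0.10 SD and the type I error about 7% to 15%; with 25% versus 15% it is at most about 0.05 SD and about 7%.

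The split by arm, the timing of loss, the shift, the correlation and the T1 effect are all assumptions. The documents therefore support a bias of unknown sign and size, not a predicted one. That uncertainty is reason enough not to rest the primary analysis on this method when a better one is already in the plan.

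**What to change.** Before the data are unblinded:

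1. Remove LOCF as the intention-to-treat method; keep it at most as a secondary analysis.
2. Make the primary analysis the likelihood-based repeated-measures model on all observed scores, with T0 in the response vector alongside T1 and T2. If T0 were only a covariate, women missing both T1 and T2 would contribute no outcome data. Multiple imputation using T0 and T1 is an acceptable alternative. Either way, every randomized woman with any score contributes.
3. State the missing-at-random assumption, and add a sensitivity analysis by delta-adjusted or control-based multiple imputation.
4. Say how women with no PHQ-9 or GAD-7 score at all are handled. Those baselines are collected after randomization, so some women may have nothing to carry forward or model.

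The cost is revised wording and some programming, with no new data or participants. Intervals will be slightly wider, because values that were never observed no longer count as data.

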### Monitoring

2.11

We have developed a data monitoring committee (DMC) to monitor conduct and quality of the trial. The DMC includes four independent members with expertise in maternal health, psychology, biostatistics and trial methodology. The DMC meeting will take place every three months.

